#### Economic evaluation

The Economic evaluation will be conducted in two ways. First, we will conduct a cost-effectiveness analysis (CEA) with treatment (i.e., UC + PT versus UC + ST) response as the clinical outcome of interest. A probabilistic medical decision-making approach is chosen, as costs are associated with large standard deviations and powering the trial for testing an economic hypothesis would require an extremely large sample size. Treatment response will be based on a binary outcome, namely the clinical outcome “depressive symptoms” (i.e., the IDS-SR score), and will be computed as a 50 % (or better) pre/12 months follow-up symptom IDS-SR reduction. Second, we will conduct a cost-utility analysis (CUA) using quality adjusted life years (QALYs, based on the EQ-5D-3 L) as a generic measure of health gains. Both the CEA and the CUA will be conducted from the societal perspective and in agreement with the ITT principle. The trial’s follow-up measurements will not exceed one year and therefore neither costs nor effects will be discounted. Sensitivity analyses will be directed at uncertainty in the main cost-drivers.

Four types of costs will be considered: (1) the costs of offering the intervention, (2) costs stemming from health care uptake including the costs of medication, (3) patients’ out-of-pocket costs, (4) costs stemming from productivity losses due to absenteeism and lesser efficiency while at work. The first two types of costs are also known as the direct medical costs and these will be based on the full economic costs of offering the training. For this we shall make use of the pertinent Dutch guideline for economic evaluation [85] and use the standard cost prices reported therein for the reference year 2014. The patients’ out-of-pocket costs are also known as direct non-medical costs and encompass the patient’s costs of travelling to health services, parking costs of the patient while travelling to and from treatment. Finally, productivity losses will be based on the mean friction costs, as outlined in the Dutch guideline for costing. Data on resource use (health care uptake) and productivity losses will be collected with the latest version of the TiC-P [79]. Importantly, in both conditions, costs of health care uptake (UC) will be evaluated. However, only in the PT condition, the costs of the intervention will be added, because that would best reflect the incremental costs of adding the new intervention onto the current package of UC and thus helps to answer the relevant question, if adding the new interventions offers good value for money.

The incremental cost-effectiveness ratio (ICER) will be computed to obtain the costs per treatment response and the costs per QALY gained. Stochastic uncertainty will be handled using 2500 non-parametric bootstraps and plotting the simulated ICERs on the ICER plane. For decision-making purposes, the ICER acceptability curve will be plotted for various willingness-to-pay (WTP) ceilings, which helps to making judgments whether the intervention offers good value for money relative to UC without PT. One-way sensitivity analyses directed at uncertainty in the main cost drivers will be performed to gauge the robustness of our findings across a range of likely values of those parameters.

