#### Randomization and blinding

Participants are randomly allocated to one of the two groups, right before the first training session. Randomization is computerized and stratified for depression severity (<39 = moderate; 39–48 = severe; > 48 = very severe) at baseline, as assessed by the Inventory of Depressive Symptomatology self-report (IDS-SR; [52]), as well as for age (18–35 years; 36–50 years; 51–65 years). In case participants indicate, that they want to discontinue with the study and withdraw consent for using their data, intervention allocation is corrected for the excluded participants.

Based on the IDS-SR score and age, the computer generates a random 5-digit number, which is linked to one of the two training conditions and which further identifies participants and their documents. This blinding code is managed by an independent statistician and revealed to researchers only, after all participants have completed the last assessment. Hence, both participants and researchers are blind to the training conditions.

To assess if participants remained blinded to their group allocation, all participants fill in an awareness check at post-test, investigating which training condition (PT or ST) they believe they have been enrolled to.

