### Procedure

Eligible patients who agreed to participate, receive a printed version of the TiC-P and are asked to fill it in at home and bring it to the baseline session (session 1). At start of this session, participants again receive written and oral information about the study. Then, they provide written informed consent and hand in the filled-in TiC-P. In a computer room, first of all, a range of disorder-related characteristics are assessed by the experimenter, including the age of onset of the depression, the number of depressive episodes during life time, the amount of psychological treatment for previous episodes, as well as information about the current episode (i.e., duration, number of psychological treatment sessions, and duration and dosage of pharmacological treatment). Afterwards, participants are seated in front of a computer, where they complete the dot-probe task (pre-assessment), which is preceded by a brief assessment of mood state (VAS). Next, they fill in computerized versions of all questionnaires (i.e., IDS-SR, STAI-T, RRS, RS, PANAS, SUIS, EQ-5D-3 L), before they complete the Stroop tasks. Finally, the PIT is administered and an appointment is made for the first training session, which again takes place at Pro Persona, within 5 days after the baseline session. Although the training is offered as web-based intervention, participants complete the very first training session under supervision of a researcher, to ensure that task instructions are well-enough understood and that the task can be completed correctly at home. The importance of completing the training by themselves, in a calm, distraction-free environment (i.e., without any music, television etc. on the background) is emphasized, both verbally and in the written task instructions. This is of particular relevance, as previous research suggests that when working memory load is high, which is likely the case in a home-environment with task-irrelevant distractions, ABM may be less or not effective [82].

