### Analyses

#### Sample size

Wells and Beevers [29] reported a large effect of ABM on change in bias (*η*
^*2*^ = .16) and on depressive symptoms (*η*
^*2*^ = .32). Likewise, Beevers et al. [35] observed a large effect for change in bias from pre- to post-ABM within the training condition (*d* = 1.01, *η*
^*2*^ = .20), but not the control condition (*d* = .04, *η*
^*2*^ = .0004). However, the above-mentioned studies were conducted in a sample of dysphoric students [29] and in a sample of treatment-seeking current MDD patients, some of whom received pharmacological treatment [35]. In the present study, ABM is provided during the waiting period for psychotherapy or in combination with pharmacological treatment and/or psychotherapy (i.e., IPT, CBT, psychiatric care). In order to account for the greater heterogeneity of our sample and because recent meta-analyses of the effects of CBM in anxiety and depression suggest rather small effects [28, 41], we conservatively assume a small to medium effect size of *η*
^*2*^ = .02 (i.e., *f* = .142). A-priori sample size is calculated with G*Power for F-tests for repeated-measures (RM) Analysis of Variance (ANOVA) with within-between interaction effects and an effect size specification as recommended by Cohen [83]. To be able to detect this effect size over two time-points, with an α-level of .05 and a power-level of .80, a total sample size of 100 would be needed, thus 50 participants per group. Compensating for an expected attrition of 20 %, we need to include 50/0.80 = 62.5, thus 63 participants per condition and *N* = 126 in total.

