### Analysis plan

#### Clinical evaluation

In accordance with the Consolidated Standards of Reporting Trials (CONSORT; [84]), all analyses of the primary and secondary outcome parameters will be carried out in accordance with the intention-to-treat (ITT) principle. Missing values due to drop-out will be imputed (e.g., by using multiple imputation (MI) or expectation maximization (EM)). Additional sensitivity analyses will be conducted to gauge the robustness of the findings, by including and excluding these participants in the analysis.

ABM effects on the primary outcome measures, attentional bias and depressive symptoms, will be tested by means of RM ANOVAs, with condition (PT, ST) as between-subjects factor and time (pre-test, post-test) as within-subjects factor. Likewise, training effects on stress responses will be investigated with a 2 (condition: PT, ST) × 3 (time: before stress, anticipatory stress, stress recovery) RM ANOVA with I PANAS-SF and STAI-S scores as dependent variables. All analyses will be conducted with and without covariates, in case variables are unevenly distributed across groups (e.g., bias or depression at baseline, number of previous depressive episodes, or number of completed training sessions), to test the robustness of the results. To investigate long-term effects of ABM on depressive symptoms, the analysis of this primary outcome parameter will be repeated over five time points (baseline, post-test, one, six, and 12 months follow-up).

Effects on secondary outcome measures will be analyzed by means of ANOVAs or ANCOVAs over two time points (baseline, post-test) in case of the cognitive transfer measures, and over four time points (baseline, post-test, one and six months follow-up), in case of rumination, positive and negative affect, and resilience.

Exploratory analyses will be directed at the process measures and will additionally be performed to take the role of potential moderators into account, such as timing of the training (i.e., during waiting period vs. next to UC) type of UC (IPT, CBT, psychiatric care), or to predict training effects based on other disorder-related characteristics assessed during baseline.

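### The economic evaluation states no adjustment of incremental QALYs or costs for the EQ-5D and TiC-P values collected at baseline; prespecifying it would gain precision at no cost

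*Protocol article*

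**What the plan says.** The Economic evaluation section plans two analyses. The cost-effectiveness analysis uses treatment response, which "will be computed as a 50 % (or better) pre/12 months follow-up symptom IDS-SR reduction". For the second analysis the text reads: "Second, we will conduct a cost-utility analysis (CUA) using quality adjusted life years", based on the EQ-5D-3L. How QALYs are derived from the repeated EQ-5D measurements is not described. On uncertainty it says: "Stochastic uncertainty will be handled using 2500 non-parametric bootstraps and plotting the simulated ICERs on the ICER plane". An acceptability curve follows, and the sensitivity analyses are directed at the main cost drivers. Baseline utility and baseline cost are not mentioned as covariates or in a sensitivity analysis.

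Both variables exist before treatment. Under Procedure, participants "receive a printed version of the TiC-P and are asked to fill it in at home and bring it to the baseline session", and at that session "they fill in computerized versions of all questionnaires (i.e., IDS-SR, STAI-T, RRS, RS, PANAS, SUIS, EQ-5D-3 L". Table 1 lists the EQ-5D-3L at T1 to T5 and the TiC-P at T1 and T5.

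Two other statements bear on the point. Under Clinical evaluation: "All analyses will be conducted with and without covariates, in case variables are unevenly distributed across groups". The examples given there are bias or depression at baseline, previous episodes and completed training sessions. Under Randomization and blinding: "Randomization is computerized and stratified for depression severity", and also for age, in three bands each.

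**The concern.** A patient's utility at baseline usually predicts later utility, and baseline cost usually predicts later cost. If the arms differ by chance at T1, a raw difference in QALYs or costs carries part of that difference into the ICER and the acceptability curve. The section itself says that costs have large standard deviations and that the trial is not powered for an economic hypothesis, so the position and spread of the bootstrap cloud will carry the decision. Using the collected baseline values would remove the part of that spread they explain.

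The covariate rule under Clinical evaluation does not settle the matter. It stands beside the repeated-measures ANOVAs, applies only if imbalance is seen, and names neither EQ-5D nor costs. Carried over as it stands, it would yield two ICERs when imbalance is observed, with no statement of which one leads.

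**Working it through.** **Plan's own figures.** The article gives no figure for QALYs, costs, the ICER or baseline imbalance. The only figure used here is the arm size. On the base sample the Sample size section says: "with an α-level of .05 and a power-level of .80, a total sample size of 100 would be needed". That N reproduces (power 0.803 with f = 0.142) if a correlation of 0.5 between time points is assumed. Then 50/0.80 = 62.5, rounded up to 63 per arm.

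**Assumptions, none of them in the article.** Equal utility SD at all visits, 0.20 to 0.30; equal correlation ρ between visits, 0.3 to 0.7; QALYs as a trapezoid area under the curve; T1 to T5 at about 0, 1, 2, 7 and 13 months; no missing data; no credit for stratification.

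**Step 1, chance imbalance in baseline utility.** SE = SD × √(2/63).
- SD 0.20: 0.036
- SD 0.25: 0.0445 (95% range ±0.087)
- SD 0.30: 0.053

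**Step 2, trapezoid weights in years.** 0.0417, 0.0833, 0.25, 0.4583, 0.25. Their sum is W = 1.0833 and the sum of squares is S = 0.3438. Baseline itself has weight w₀ = 0.0417.

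**Step 3, formulas.**
- Slope of QALY on baseline utility: b = w₀ + ρ(W − w₀)
- Variance of QALY in units of SD²: V = (1 − ρ)S + ρW²
- Share of variance removed by adjustment: R² = b²/V
- SE of the unadjusted difference: SD × √(2V/63); adjusted: that value × √(1 − R²)

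**Step 4, worked case (SD 0.25, ρ = 0.5).**
- b = 0.0417 + 0.5 × 1.0417 = 0.5625
- V = 0.5 × 0.3438 + 0.5 × 1.1736 = 0.7587
- R² = 0.3164/0.7587 = 0.417
- Shift from a 1-SE imbalance: 0.5625 × 0.0445 = 0.025. Of this, 0.0417 × 0.0445 = 0.002 is the direct weight of the baseline value; the rest comes through correlation with later visits.
- SE falls from 0.039 to 0.030.

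In this case a 1-SE imbalance equals 0.025/0.039, about 0.65 of an SE of the QALY difference. With no true effect and no other error, about 74% of bootstrap replicates would then show a QALY gain, where 50% would be expected.

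**Step 5, range.**

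| ρ | b | R² | Shift per 1 SE, SD 0.20 to 0.30 | SE at SD 0.25, unadjusted → adjusted |
|---|---|---|---|---|
| 0.3 | 0.354 | 21% | 0.013 to 0.019 | 0.034 → 0.030 |
| 0.5 | 0.563 | 42% | 0.020 to 0.030 | 0.039 → 0.030 |
| 0.7 | 0.771 | 64% | 0.028 to 0.041 | 0.043 → 0.026 |

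The section says that follow-up will not exceed one year. Placing T5 at 12 months changes little: shift 0.012 to 0.038, variance reduction 22% to 65%. With 50 completers per arm, all SEs and shifts rise by √(63/50) = 1.12 and R² is unchanged.

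**Costs.** The article gives no cost SD and no correlation between baseline and follow-up cost, so no figure can be computed.

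**The case against.** The strongest reply is that the article never says the increments will be unadjusted. A bootstrap describes uncertainty and is compatible with any estimator, including a regression-adjusted one. The article condenses a fuller plan that is not shown, and covariates in an economic model are commonly set there. The covariate sentence speaks of all analyses with open-ended examples, and the abstract lists quality of life and costs among the secondary outcomes, so it could be read to cover them. This stands in part. A reader might infer a commitment to an unadjusted ICER, and the text does not support that. It supports only that the section describes the analysis in some detail and leaves this element out.

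A reader might also infer that the ICER would be biased. Under randomization, chance imbalance does not bias the increment on average, and it is already part of the spread that the bootstrap shows. What adjustment removes is error conditional on the imbalance that actually occurred, together with avoidable variance.

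Third, it is tempting to say that such imbalance is as large as the QALY gain the trial could show. The article states no expected QALY gain, so that comparison cannot be made.

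Stratification on IDS-SR severity should limit utility imbalance, and the figures above give no credit for it. It works in broad bands and does not target costs, so it reduces the point without removing it.

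**Conclusion.** The point holds as a no-cost improvement to the analysis, and it does not show an error in the plan. The article states no baseline adjustment for incremental QALYs or costs, and its only covariate rule does not clearly apply to them. Under the assumptions listed, a 1-SE chance imbalance in baseline utility moves the unadjusted QALY difference by about 0.012 to 0.041, and adjustment would reduce the variance of that difference by about 21% to 64%. These sizes rest wholly on the assumed SD, correlation and area-under-the-curve QALY. For costs only the direction of the argument can be given. The response outcome of the cost-effectiveness analysis is already relative to baseline IDS-SR, so there the point reaches the cost increment only.

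**What to change.** Before the allocation code is revealed, confirm that the full analysis plan contains the following, or add it:

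- Draw each of the 2500 bootstrap samples within arm, keeping each patient's costs and effects together.
- In each sample, estimate incremental QALYs by regression on arm, baseline EQ-5D and the stratification factors (IDS-SR severity, age).
- In the same sample, estimate incremental costs by regression on arm, baseline TiC-P cost and the same factors. The two equations may be fitted jointly, for example by seemingly unrelated regression.
- Form the cost-per-QALY ICER, the ICER plane and the acceptability curve from the adjusted increments.
- In the cost-effectiveness analysis, use the adjusted cost increment and leave the response outcome as defined.
- Report the unadjusted result as a sensitivity analysis. Adjust whether or not imbalance is observed.

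The cost is a few sentences of analysis wording. All variables are already collected, and no visit, sample size or procedure changes.

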Despite these somewhat mixed results and limited number of studies, above-mentioned research suggests, that ABM might be of therapeutic value for depression and may have the potential to increase response and remission rates, achieved by usual care (UC). Considering the growing acknowledgement of the importance of self-help interventions as adjunct to regular health care in depression [36] and promising findings from numerous studies on the effectiveness of computer-therapy for this disorder (for a meta-analysis, see [37, 38]), the idea would be very appealing to add ABM as internet-based intervention to existing treatment services. As ABM consists of a rather simple and straightforward computer task and thus needs no or minimal assistance of a clinician, it may flexibly be incorporated into patients’ everyday life, being accessible 24 h a day, on every day of the week. Moreover, the training can be followed at home, in a familiar environment and is not associated with any travel time and costs. Due to these advantages, ABM may be provided to patients not only parallel to UC, but would also be accessible during waiting period for treatment. ABM thus might offer patients and effective, acceptable and budgetary affordable intervention to start with immediately after being referred to mental health care and bridge the, due to insufficient treatment capacitates in the health care system, often unacceptable long time between referral and start of treatment (i.e., up to 90 days or more;[39]). Next to the potential therapeutic effects, the addition of ABM on top of regular treatment may have favorable economic impacts through reducing the number of sessions of outpatient care by accelerating speed of recovery. This in turn may reduce down-stream costs and may further positively affect return-to-work and productivity.

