During the first training session (session 2), participants receive written and verbal practical information regarding the online training-program. They then complete the first training which is, like all dot-probe trainings, flanked by brief mood state measures (VAS). Afterwards, the CEQ is administered and appointments are made for the seven training sessions (session 3–9), as well as for the post-assessment (session 10). The eight training sessions are distributed across two weeks, with four weekly sessions. During the two weeks of training, participants receive automated e-mails reminding them of the planned sessions. In case, participants do not complete the planned sessions, even though they have been reminded by e-mails, they are given a call by the experimenter who asks them to still complete the session. The post-assessment, which again takes place at Pro Persona, is scheduled at least one week and a maximum of two weeks after the last training session. The post-assessment is comparable to the baseline assessment but without the Tic-P and the RS, and with the additional speech task. Afterwards, appointments are made for the subsequent follow-up assessments and participants receive a reimbursement for their travel cost (15 Euros).

During the first two follow-up assessments (session 11 & 12), participants complete questionnaires via the internet (IDS-SR, STAI-T, RRS, RS, PANAS, EQ-5D-3 L). At 12 months follow-up (session 13), the MINI is administered via telephone to assess the diagnostic status of depression. Moreover, participants complete the IDS-SR, EQ-5D and Tic-P via internet. After having filled in the questionnaires, participants receive a debriefing form with contact information of the coordinating investigator, who can be contacted in case of questions. The use of medication as well as the number of psychological treatment sessions is monitored at the post-test and all follow-up measures. For an overview of all measures and corresponding time points, see Table 1.

**Table 1 Tab1:** Overview of all measures and corresponding time points

Domain	Target Concept (Measure)	T0	T1	Training 1	Training 2–8	T2	T3	T4	T5
Screening measures	Inclusion Criteria Interview	•							
	Diagnostic status (MINI)	•							•
Primary outcome measures	Attentional Bias (Dot-probe)		•			•			
	Depressive Symptomatology (IDS-SR)		•			•	•	•	•
	Mood response and recovery from speech task (I PANAS-SF & short STAI-S)					•			

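### One TiC-P after randomisation, at 12 months, is the only named source of productivity losses, unmonitored care and its travel costs in both 12-month societal ICERs

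*Protocol article*

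**What the plan says.** **What the costs are for.** The protocol article, Economic evaluation, plans a cost per treatment response and a cost per QALY: "Both the CEA and the CUA will be conducted from the societal perspective and in agreement with the ITT principle". Response compares baseline with 12 months, and QALYs come from the EQ-5D. The cost types are the intervention, health care uptake including medication, out-of-pocket costs, and productivity losses from absence and reduced efficiency at work. The named source for resource use and productivity is given there: "Data on resource use (health care uptake) and productivity losses will be collected with the latest version of the TiC-P".

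**When the TiC-P is given** (Procedure):
- Baseline (T1): patients "receive a printed version of the TiC-P and are asked to fill it in at home and bring it to the baseline session". Randomization and blinding places allocation later, directly before the first training session.
- Post-assessment (T2): "The post-assessment is comparable to the baseline assessment but without the Tic-P and the RS, and with the additional speech task".
- 1 and 6 months (T3, T4): "participants complete questionnaires via the internet (IDS-SR, STAI-T, RRS, RS, PANAS, EQ-5D-3 L". The TiC-P is not listed.
- 12 months (T5): "Moreover, participants complete the IDS-SR, EQ-5D and Tic-P via internet".

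Table 1 agrees, with two marks for the TiC-P and five for the EQ-5D.

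**What else is recorded.** Procedure also has medication use and the number of psychological sessions monitored at T2 to T5. Recruitment says that health care consumption is followed closely in both arms, but gives no instrument or timetable. The article states no TiC-P recall window and no rule for filling gaps between T1 and T5.

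**The concern.** A cost over 12 months is a sum over time, so it needs data that cover the whole period. The T1 report describes the time before randomisation and says nothing about what the arms cost afterwards. That leaves T5 as the only TiC-P with information on the comparison.

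The economic argument in Background has two strands. One is "reducing the number of sessions of outpatient care by accelerating speed of recovery", the other is earlier return to work and better productivity. The first has interim records. The second has none named. If absence or other care differs between arms in a part of the year that T5 does not reach, the incremental cost in both ICERs and both acceptability curves will not describe the year that the effects describe. Bootstrapping reflects sampling variation, and one-way sensitivity analyses vary the cost drivers. Neither supplies months that were never measured, and no later analysis plan can do so either.

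**Working it through.** The article gives no cost figure and no recall window, so there is no planning figure to reproduce. The check has four steps.

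**1. Which cost items have a source between T1 and T5?**

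| Item | Named source after randomisation |
|---|---|
| Medication | Monitored at T2, T3, T4, T5; TiC-P at T5 |
| Psychological sessions | Monitored at T2, T3, T4, T5; TiC-P at T5 |
| Travel and parking for those sessions | Could be estimated from the session counts |
| Other care and travel to it | TiC-P at T5 only |
| Absenteeism | TiC-P at T5 only |
| Reduced efficiency at work | TiC-P at T5 only |

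The general remark in Recruitment might cover other care, but it names no instrument. The Economic evaluation section does not link any of the monitoring to the costing.

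**2. How much of the year does T5 observe for the last three rows?** Assume a recall window of w months. The year is taken as 12 months, ignoring the two training weeks. Share observed = w / 12.
- w = 1: 1/12 = 8% observed, 92% not
- w = 3: 3/12 = 25% observed, 75% not
- w = 6: 6/12 = 50% observed, 50% not
- w = 12: 12/12 = 100% observed, all from one recall reaching back a year

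**3. What happens if a shorter window is scaled up to a year?** The estimate is (difference seen in the window) × 12 / w. Let the arms differ by S per month in these items. The three timings are illustrations, not predictions.
- Difference in months 1 to 6 only, true total 6S: any window of 6 months or less sees 0 and returns 0.
- Difference in months 7 to 12 only, true total 6S: a 6-month window sees 6S and returns 6S × 12/6 = 12S, twice the truth.
- Constant difference all year, true total 12S: a 6-month window returns 6S × 12/6 = 12S, which is correct.

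Scaling is right only if the difference is constant over the year. Interpolating from T1 to T5 does not help, because T1 carries no treatment difference.

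**4. What would extra measurements cover?** With the TiC-P at T3, T4 and T5 and each window running back to the previous measurement, the intervals are 1 + 5 + 6 = 12 months. With T4 and T5 only, they are 6 + 6 = 12 months. Either way the longest recall is 6 months. Adding time points with a fixed short window is not enough: at T3, T4 and T5 a 1-month window covers (1 + 1 + 1)/12 = 25%, and a 3-month window (1 + 3 + 3)/12 = 58%.

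**The case against.** The strongest reply is that the recall window belongs to a cited instrument that is not shown, and a condensed article may leave it to the full protocol. With a 12-month window there is no coverage gap, and the issue is only the quality of recall. This stands. A reader might infer that the 12-month societal cost cannot be derived at all. The article does not support that: it depends on the window, and even under a short window it does not apply to every component.

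Second, a reader might infer that savings from fewer sessions would be lost. They need not be, because session counts and medication are recorded at four points after training. What is missing is the statement that the costing will use them.

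Third, a reader might infer that savings come early and are therefore missed. Background does speak of faster recovery, but Background, Aim and hypotheses, and Discussion all expect symptom effects to emerge over a longer time. The timing is open, and the gap matters wherever a difference falls before the T5 window.

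Fourth, the richer EQ-5D schedule helps only the cost-utility analysis. Response in the cost-effectiveness analysis uses baseline and 12 months, the same two points as the TiC-P. That is true, but two points suffice for a change in status and not for an accumulated cost.

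Fifth, patients and researchers are blinded, so recall error should not depend on knowledge of allocation. Under a 12-month window one would mainly expect noise or attenuation, not a clear bias in one direction.

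What remains is that absence, reduced efficiency, other care and travel to it are either partly unobserved or recalled once over a year.

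**Conclusion.** The point holds, limited to the items without a named interim source. Text and table agree that T5 is the only TiC-P after randomisation, and the plan puts its content into both 12-month societal ICERs. For absenteeism, reduced efficiency at work, other care and travel to it, 50% to 92% of the year is unobserved if the window is between 6 months and 1 month. Nothing is unobserved if the window is 12 months, but the whole amount then depends on one long recall. These windows are assumptions, since the article states none.

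Medication and psychological session costs lie outside the problem provided that the T2 to T5 records are used. The direction of any error in the incremental cost cannot be given, because it depends on when the arms differ. The clinical outcomes are not affected. This is a cheap improvement to the economic part, not a flaw that invalidates it.

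**What to change.** - Add the TiC-P resource-use and productivity sections to the existing internet session at 6 months, and preferably also at 1 month.
- State the recall window at each point and let it run back to the previous measurement, with the first reaching back to randomisation. Check that the TiC-P version in use allows this. If it does not, document the adaptation.
- Sum the intervals to a 12-month cost per patient before bootstrapping.
- Name the T2 to T5 medication and session records as a costing source, and say how they are combined with the TiC-P so that nothing is counted twice.

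The cost is an amendment and one or two more online questionnaires in sessions that patients already complete, hence somewhat more patient burden. No extra visits or staff are needed. Recall of five to six months remains, which is shorter than a year but not short.

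If follow-up is too far advanced, state the T5 window. Limit the cost claim to the period that the T5 TiC-P observes plus the monitored medication and sessions, and do not report the result as a full 12-month societal cost.
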